## Sample size

We assume that a sample size of 60 participants is large enough to determine feasibility [38]. The information from this pilot trial will inform the design and provide initial estimates of effect for sample size calculation for the main trial.

## Data collection and management

Data collection tools will include a baseline questionnaire and a follow-up questionnaire (at weeks 2, 6, 10, and 24 post randomization). Our questionnaires were developed using a validated WHO infant feeding questionnaire [39]. The questionnaires will be used in English and will be administered by a research nurse or counsellor fluent in the participant’s language. In instances where study participants speak only local languages, the researcher nurse will translate questions directly. We will inquire about feeding practices during the previous 24 h and during the prior week. Study follow-up, SMS messages, and responses will be recorded on a study log weekly. Telephone communications with participants in the usual care group not receiving text messages will be recorded in a similar study log. Clinic records will be reviewed for clinically relevant data. Study follow-up will continue until complete cessation of breastfeeding or until end of study.

To maintain participant confidentiality, only a coded number will identify all questionnaires, reports, and other records. A unique patient identification number will be used to link participant-specific data. All paper records will be kept in a locked file cabinet at the research site and at the Centre for Evidence Based Health Care, Stellenbosch University. Access will be limited to research staff. Electronic files will be password-protected. Clinical information will not be released without written permission of the participant, except if required by the ethics review committee. Participant names will be stored separately. No reports will link individual names with person level data. The research nurse or counsellor will receive training prior to beginning of the trial. A standard operations manual will be available to staff for reference on operational details.

Data will be transcribed from the paper format into an electronic database. We will check data to ensure that entered values are acceptable, required fields are completed, and items are consistent with other related items in the database. We will verify with source documents for any discrepant entries. A record of the database update will be kept, identifying information about the person who made the changes, date, changed values, and comments.

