### Mobile phone text messaging

Consented new mothers will register their phone numbers into an automated text message (SMS) software (provided by WelTel.org). The first SMS will be sent within the first week following delivery. Every Monday morning, a text message will be sent to women in the intervention group encouraging them to exclusively breastfeed and inquire if they have any problems breastfeeding their infants. Participants will be asked to respond by text within 48 h, indicating that they either do not have a problem or they have a problem and require help. Participants may also use the free ‘call back’ function to request a call from the nurse for complex issues or if cost or literacy is a problem. The research nurse will review all the responses and then follow-up and provide triage to any participants who indicate a problem or call participants who fail to respond within 48 h. To preserve confidentiality, the content of the text messages will not be related to the woman’s HIV status. Participants will be briefly trained on use of the phone and the text messaging protocol.

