### Motivational interviewing

In addition to text messaging, women will have individual motivational interviews post delivery at weeks 2, 6, and 10. Study visits will be in line with the Expanded Program of Immunization routine schedule to maximize participation [37]. We will train the research nurse in motivational interviewing techniques, which include reflective listening and expression of acceptance and affirmation. These techniques will enable the research nurse to understand participant’s frame of reference, reinforce participant’s own self-motivational statements, monitor the readiness to change, and affirm the participant’s freedom of choice. Advice will be given with participant’s permission, and when given, the participant will make her own choice. The research nurse will apply these techniques considering the participant’s readiness to change. The interviews will be recorded.

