### Secondary endpoints

Secondary outcomes include number of participants who are exclusively breastfeeding 24 weeks post delivery and number of participants who are breastfeeding. This will be assessed using a questionnaire of food items given to the baby in the last 24 h and one week preceding inquiry. Participants will be considered either “adherent” to exclusive breastfeeding if babies receive only breastmilk and no other liquids or solids based foods or “non-adherent” if other foods are given. Breastfeeding will be assessed by self-report of women who report breastfeeding in addition to giving other foods. Study outcomes will be evaluated at weeks 2, 6, 10, and 24.

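### The research nurse who delivers the intervention may also administer, and is told to translate live, the self-report feeding questionnaire, which could inflate reported adherence more in the intervention arm

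*Protocol article*

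**What the plan says.** **Delivery.** The protocol article gives the personal part of the intervention to the research nurse. Under Mobile phone text messaging, "The research nurse will review all the responses and then follow-up and provide triage to any participants who indicate a problem"; the nurse also phones women who have not answered within 48 h. The weekly message itself is automated: women "will register their phone numbers into an automated text message (SMS) software". Under Motivational interviewing, "We will train the research nurse in motivational interviewing techniques", and "women will have individual motivational interviews post delivery at weeks 2, 6, and 10".

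**Measurement.** Under Secondary endpoints, adherence is the mother's account of what the baby was fed in the last 24 h and the last week, and "Study outcomes will be evaluated at weeks 2, 6, 10, and 24". Under Data collection and management, the questionnaire "will be administered by a research nurse or counsellor fluent in the" participant's language. For women who speak only local languages, "the researcher nurse will translate questions directly".

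**Blinding and usual care.** The Randomization scheme and Ethical aspects sections blind data analysts only. Under Usual standard of care, control women are counselled on exclusive breastfeeding by primary healthcare nurses and lay counsellors.

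**Use of the result.** Adherence of at least 70% in the intervention group at 24 weeks is a feasibility criterion (Primary endpoints). The Sample size section intends the effect estimates for sizing the main trial.

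**The concern.** A woman asked what she feeds her baby by the nurse who has been phoning and motivating her to breastfeed may be reluctant to admit to other foods. The plan permits this arrangement and does not separate the two roles. For women who speak only local languages it goes further and makes the unblinded nurse the translator, so the wording of the outcome questions can vary from woman to woman.

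A usual-care woman may feel some of the same pressure, but the plan does not give her the same series of contacts with the research nurse. If over-reporting is greater in the intervention arm, the 70% criterion becomes easier to meet and the apparent effect grows. An inflated effect carried into main-trial planning would make that trial too small. The Discussion concedes that self-report is not an objective measure, but mentions neither the dual role nor a possible difference between arms.

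**Working it through.** **Roles set side by side (protocol article)**

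| Task | Who | When |
|---|---|---|
| Review replies, triage, call non-responders (intervention arm) | Research nurse | Weekly |
| Motivational interview (intervention arm) | Research nurse | Weeks 2, 6, 10 |
| Feeding questionnaire (both arms) | Research nurse or counsellor | Weeks 2, 6, 10, 24 |
| Live translation (either arm, if needed) | Research nurse | At the questionnaire |
| Breastfeeding counselling (usual care) | Primary healthcare nurses, lay counsellors | Includes study visits if concerns are reported |

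Three of the four assessments fall in interview weeks. Week 24, where the 70% criterion is judged, does not.

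**Numbers of women**
- Stated sample size: 5 per week × 12 weeks = 60, which matches the plan.
- 1:1 allocation: 60 / 2 = 30 per arm.
- Pass mark: 0.70 × 30 = 21 women.

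**Shift in the criterion.** The document gives no over-reporting rate, so these are assumptions.
- 1 over-reporter: 1/30 = 3.3 points. 4 over-reporters: 4/30 = 13.3 points.
- Three over-reporters turn 18/30 = 60% (fail) into 21/30 = 70% (pass).

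**Chance of passing.** Let t be the true adherence rate and m the share of non-adherent intervention women who report adherence, both assumed. The observed rate is p = t + (1 − t)m, and the chance of passing is P(X ≥ 21) for X ~ Binomial(30, p).

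| t | m = 0 | m = 10% | m = 20% | m = 30% |
|---|---|---|---|---|
| 50% | 2.1% | 6.9% | 17.6% | 35.8% |
| 60% | 17.6% | 31.6% | 49.4% | 68.1% |
| 65% | 35.8% | 51.8% | 68.1% | 82.1% |

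At t = 60% there are 12 non-adherent women, so m = 10% to 30% means 1.2 to 3.6 women, within the 1 to 4 range above.

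**Between-arm estimate with no real effect (both arms truly 50%)**
- Only the intervention arm over-reports, at 10%, 20% or 30%: p = 0.55, 0.60 or 0.65, and the odds ratio against 0.50/0.50 is 1.22, 1.50 or 1.86.
- Both arms over-report, usual care at 10% and intervention at 20%: (0.60/0.40) / (0.55/0.45) = 1.50 / 1.22 = 1.23.
- Both arms over-report equally: odds ratio 1.

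The comparison is therefore distorted only by a difference in over-reporting between arms. The 70% criterion uses one arm, so any over-reporting there moves it.

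**The case against.** **One-arm bias.** A reader might infer that over-reporting acts on the intervention arm alone. The document does not support that. Usual-care women are also urged to breastfeed exclusively, and live translation applies to women in either arm. The counsellor who may administer the questionnaire could be one who counsels usual-care women; the document does not say. Only a difference in degree can be argued.

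**Certain direction.** A reader might also infer that adherence is bound to be overstated. The interviewing style described, accepting and respectful of the woman's choice, could make it easier to admit to other foods. Over-reporting is plausible but not shown, and its size is assumed throughout.

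**Week 24.** No interview is scheduled then, so asking the questions first cannot help at the visit that decides the 70% criterion. This is correct and shapes the fix.

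**Operational detail.** Task order could sit in the operations manual, which is not shown, and staff training could cover it. This stands in part, so the absence of an ordering rule is a weak point taken alone. But the article itself names who administers and who translates, and that choice permits the overlap.

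**Pilot status.** Effects are of secondary interest. That limits the weight of the point, but adherence is a formal success criterion and the estimates are meant for later planning.

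Blinded analysts do not answer the concern, because the answers are already given. Nor does best- and worst-case imputation, which deals with missing answers and not inaccurate ones.

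**Conclusion.** The point holds as an avoidable risk of measurement bias. As written, the plan lets the person delivering the intervention collect its unblinded self-report outcome, and makes that person the live translator. Over-reporting may occur in both arms and may be greater in the intervention arm. It could then inflate the 70% criterion and the effect estimates for the main trial.

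The size cannot be found from the document. Under the assumption of 1 to 4 over-reporters among 30 women, the shift is 3 to 13 points. The pass probabilities and odds ratios above are illustrations on the same footing. Recruitment, consent and completeness criteria are not affected. The point supports inexpensive improvements to data collection; it does not show that the adherence result will be invalid.

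**What to change.** In Data collection and management:

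1. At weeks 2, 6 and 10, complete the feeding questionnaire in both arms before any motivational interview or counselling at that visit. This removes influence within the visit, though not that of earlier contacts.
2. Replace live translation with fixed written translations of the feeding items in the local languages used, for both arms.
3. Where existing staffing allows, and above all at week 24, have the questionnaire administered in both arms by existing staff who counsel neither arm. Naming simply the counsellor would not be enough: if that person counsels usual-care women, the bias could move to that arm. Where no such person is available, record who administered each questionnaire and report adherence by assessor.

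In the Discussion, state the dual role as a limitation, separately from the general remark on self-report.

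The cost is some loss of scheduling flexibility and a small translation effort, possibly in more than one language. Item 3 is conditional so that it does not require new posts. Trial status says recruitment has not begun, so all of this can be in place before the first participant.

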## Analysis plan

### Primary outcomes

Analysis of baseline characteristics and feasibility outcomes will be based on descriptive statistics reported as percentages (95% confidence intervals [CI]) for categorical variables and mean (standard deviation) or median (interquartile range) for continuous variables depending on the distribution.

### Secondary outcomes

We will follow the Consolidated Standards of Reporting Trials (CONSORT) extension for reporting pilot trials [40]. We will use the intention-to-treat principle for secondary outcome analysis, where all participants randomized will be considered per group assignment. In this analysis, we will impute missing outcome data using both the best-case and worst-case scenario. For adherence outcomes, missing data at study visits will be considered as “adherent” and “non-adherent,” respectively. For breastfeeding outcome, missing data at study visits will be considered as “stopped breastfeeding” and “still breastfeeding.” The study is not adequately powered to test intervention effects and these will be of secondary interest to assess potential trends. Logistic regression models will be built for binary outcomes. For timed endpoints, the cumulative proportions of women stopping exclusively breastfeeding and cumulative proportions of those stopping any breastfeeding, we will use the Kaplan–Meier survival analysis followed by multivariable Cox proportional hazards model to adjust for possible baseline imbalances. We will report odds ratios and hazard ratios (95% CI) as initial estimates of effect. Table 1 provides a summary of methods of analysis for each variable. Separately, we will conduct sub-analysis to assess subgroup effects, a summary of this analysis follows below.

**Table 1 Tab1:** Variables, measures, and methods of analysis

Variable/Outcome	Type	Hypothesis	Outcome measure	Method of analysis
l. Primary				
a. Participants recruited	Count		Percentage recruited	Descriptive statistics
b. Participants consenting	Count		Percentage consenting	Descriptive statistics
c. Completeness of evaluation of outcomes	Count		Percentage with complete outcome evaluation	Descriptive statistics
d. Cumulative breastfeeding adherence at six months	Binary		Percentage adherence in the last 24 h and 1 week	Descriptive statistics
2. Secondary				
a. Adherence to exclusive breastfeeding	Binary	SMS + motivational interview leads to better adherence to breastfeeding than usual care	Percentage adherence in the last 24 h and 1 week	Logistic regression
b. Time to stopping breastfeeding	Time-to-event	SMS + motivational interview prolongs time to stopping breastfeeding than usual care	Reporting of complete cessation of breastfeeding	Kaplan–Meier survival analysis

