## Randomization scheme

Participants will be randomly assigned to study groups using a permuted block method. The randomization sequence will be generated using a random number generating program, with a 1:1 allocation ratio with blocks of different sizes to ensure a balanced allocation. Block sizes will be randomly permuted. Electronic sequence generation and random allocation will be done centrally. Women meeting inclusion criteria who consent to participate will be enrolled and immediately assigned a study arm in sequential order. The principal investigator will coordinate the procedures. Only data analysts will be blinded to participant allocation.

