### Primary endpoints

The primary feasibility outcomes will include the number of participants invited to participate in the study who consent to participate, number of participants with complete evaluation of infant feeding practices at all study visits as assessed by the infant feeding questionnaire, and the number of involuntary disclosures of HIV status due to text messaging. Criteria for feasibility success will include:five participants recruited per week (i.e. 60 participants over 12 weeks);about 75% of all eligible participants consent to participate;complete evaluation of outcomes in at least 70% of all recruited participants;breastfeeding adherence rate of at least 70% in the intervention group, at 24 weeks post delivery;number of participants reporting involuntary disclosure of HIV status due to text messaging less than 5%.

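### Best-case and worst-case imputation ignores arm, so it bounds each arm's proportion but not the between-arm effect; the breastfeeding labels are also in reverse order

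*Protocol article*

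**What the plan says.** The rule is in the protocol article, Analysis plan, Secondary outcomes. The intention-to-treat set is everyone randomized: "all participants randomized will be considered per group assignment". Within that analysis "we will impute missing outcome data using both the best-case and worst-case scenario".

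Two sentences then fix the values. The first reads "For adherence outcomes, missing data at study visits will be considered as “adherent” and “non-adherent,” respectively". The second begins "For breastfeeding outcome, missing data at study visits will be considered as" and gives first the state of having stopped, then the state of still breastfeeding. Neither sentence mentions study arm, and no other section adds a version that does.

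The same section says that odds ratios and hazard ratios with 95% confidence intervals will be reported as initial estimates of effect. The Sample size section says that the pilot will supply initial effect estimates for the main trial's sample size calculation. The Primary endpoints section counts as a success "complete evaluation of outcomes in at least 70% of all recruited participants".

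**The concern.** A best-case and worst-case pair is normally read as showing how far the missing data could move the result. The result of interest here is a comparison of two arms. If all missing women in both arms are set to the same value, the two arms move together and most of the movement cancels in the comparison. The pair can then look tight when the data are compatible with a much wider range of effects, including harm.

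If missingness differs by arm, the labels can also point the wrong way. Setting everyone missing to non-adherent penalises the arm with more missing women. If that is usual care, the scenario called worst shows the larger benefit. Unequal missingness is plausible, because only the intervention arm gets weekly messages and calls to women who do not reply.

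What is at stake is the planning of the main trial: a misleadingly narrow range around the effect estimate that is to inform its sample size.

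The second, smaller problem is the order of the breastfeeding labels. Table 1 hypothesises that the intervention prolongs breastfeeding, so still breastfeeding is the favourable state. It is nevertheless listed second, where the preceding sentence puts the worst case.

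**Working it through.** **Inputs from the protocol.** The sample size is 60 ("We assume that a sample size of 60 participants is large enough to determine feasibility"), which agrees with the recruitment criterion: 5 per week x 12 weeks = 60. Allocation is "with a 1:1 allocation ratio with blocks of different sizes to ensure a balanced allocation", so about n = 30 per arm. The completeness criterion allows up to 30% incomplete: 0.30 x 60 = 18, or 9 per arm if split evenly.

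**Assumed inputs.** The protocol gives no observed counts and no expected missingness at a given visit. All adherent counts and all missing counts by arm below are assumptions.

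**Algebra.** Let a and c be the women observed adherent in the intervention and control arms, and M1 and M0 the numbers missing.

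- All missing adherent: RD = (a + M1 - c - M0)/n
- All missing non-adherent: RD = (a - c)/n
- Distance between the two written scenarios: |M1 - M0|/n
- Intervention favourable, control unfavourable: RD = (a + M1 - c)/n
- Intervention unfavourable, control favourable: RD = (a - c - M0)/n
- Distance between these opposite-direction extremes: (M1 + M0)/n

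The written pair therefore spans the difference in missingness, and the extremes span the sum. The two coincide only if all missing data fall in one arm.

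**Main illustration: 9 missing per arm, 15/21 v 11/21 observed.** The observed difference is 15/21 - 11/21 = +19.0 points.

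| Scenario | Counts | Risk difference | Odds ratio |
|---|---|---|---|
| All adherent (as written) | 24/30 v 20/30 | +13.3 points | (24 x 10)/(6 x 20) = 2.00 |
| All non-adherent (as written) | 15/30 v 11/30 | +13.3 points | (15 x 19)/(15 x 11) = 1.73 |
| Intervention favourable, control unfavourable | 24/30 v 11/30 | +43.3 points | (24 x 19)/(6 x 11) = 6.91 |
| Intervention unfavourable, control favourable | 15/30 v 20/30 | -16.7 points | (15 x 10)/(15 x 20) = 0.50 |

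The written pair has width 0 on the risk difference and runs from 1.73 to 2.00 on the odds ratio. The extremes are 60 points apart and run from 0.50 to 6.91.

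**Range over other assumed missingness (30 per arm).**

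| Missing, intervention / control | Observed adherent | Written: all adherent, all non-adherent | Opposite-direction extremes |
|---|---|---|---|
| 3 / 3 | 19/27 v 13/27 | +20.0, +20.0 points (OR 2.41, 2.26) | +10.0 to +30.0 points (OR 1.51 to 3.60) |
| 6 / 12 | 17/24 v 9/18 | +6.7, +26.7 points (OR 1.41, 3.05) | -13.3 to +46.7 points (OR 0.56 to 7.67) |
| 12 / 6 | 13/18 v 12/24 | +23.3, +3.3 points (OR 3.33, 1.15) | -16.7 to +43.3 points (OR 0.51 to 7.50) |
| 9 / 0 | 15/21 v 15/30 | +30.0, 0.0 points (OR 4.00, 1.00) | 0.0 to +30.0 points (OR 1.00 to 4.00) |

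The 6 / 12 row shows the inverted labels: the worst case gives +26.7 points and the best case +6.7.

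**Labels.** For adherence, the order is favourable then unfavourable, tied to best and worst by an explicit word of correspondence. For breastfeeding, the order is unfavourable then favourable, with no such word. Read in parallel, stopping becomes the best case.

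**The case against.** The strongest reply is that the protocol never claims that the scenarios bound the treatment effect, and never says outright that both arms are treated alike. The scenarios do bound each arm's own proportion. This is a condensed article, and arm-specific detail could sit in a fuller plan. The first two statements are true. But the text is not silent: it fixes a value for each scenario without reference to arm, inside the analysis that compares the arms. The literal rule is therefore open to comment.

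Other parts of the reply stand and limit the point. A reader might infer that the written pair shows no sensitivity at all. That holds only for the risk difference with equal numbers missing, whereas the protocol reports odds and hazard ratios. In the main illustration the odds ratio does move, from 2.00 to 1.73. A reader might also infer that both scenarios always pull the effect towards zero. They do not: in the 6 / 12 case the observed difference is 17/24 - 9/18 = +20.8 points, and the all-non-adherent scenario raises it to +26.7.

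Nor does the 70% criterion mean that 30% will be missing at week 24. The Primary endpoints section defines completeness over all study visits, so a woman who misses only week 6 counts as incomplete but still has a week-24 outcome.

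Two further complaints do not hold as findings. Confidence intervals that treat imputed values as observed are a feature of any single-value extreme scenario, including the ones proposed here. The choice of a main estimate by multiple imputation, and the censoring rule, can be left to the analysis plan and are debatable in a pilot of 60 women.

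**Conclusion.** The point holds in limited form. As written, the two scenarios bound each arm's proportion but not the between-arm effect. On the risk-difference scale they span the difference in missingness between arms, where the extremes span the sum. With equal missingness the odds ratio also moves little. With 9 missing per arm and the assumed counts, the gap is 0 against 60 points. With 3 missing per arm it is 0 against 20 points, and the extremes no longer cross zero. These sizes rest on assumed counts, and 9 per arm is the adverse end of what the completeness criterion allows.

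The label reversal is real but probably a slip of wording. A reader might infer that it corrupts the breastfeeding results. It does not: both values are run, so it would mislabel results without changing a number.

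Importance is moderate to low. The rule is stated for secondary outcomes only, the primary feasibility outcomes are analysed descriptively, and the protocol says that the trial is not powered for intervention effects. It still deserves correction, because the effect estimates are intended to feed the main trial's sample size.

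**What to change.** Add two scenarios in opposite directions to the Secondary outcomes section:

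- missing intervention women set to adherent or still breastfeeding, with missing control women set to non-adherent or stopped;
- the reverse.

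Report these as the bounds on the odds ratios and hazard ratios. The existing pair can stay as bounds on each arm's own proportion, described as such. No hazard-ratio figures are given above, because the protocol has no event-time data to compute them from.

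Reorder the breastfeeding sentence so that still breastfeeding is the best case and stopped is the worst, with the same explicit correspondence as in the adherence sentence.

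Blinding of the analysts is not affected: they can run both directions with coded arms, and the labels are attached when the code is opened. The cost is a little more programming and a wider reported range. The article states that recruitment had not started, so the change could be made before any data were collected.

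### Table 1 calls the 70% adherence outcome cumulative, but recalls at weeks 2, 6, 10 and 24 give point prevalence and cannot date the stopping of exclusive breastfeeding

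*Protocol article*

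**What the plan says.** Table 1 in the Analysis plan lists, as primary row 1d, "Cumulative breastfeeding adherence at six months Binary Percentage adherence in the last 24 h and 1 week". The Primary endpoints section gives the criterion this row serves: adherence of at least 70% in the intervention group at 24 weeks after delivery. The abstract likewise places it six months after delivery.

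The measure is described in two further places. Secondary endpoints refers to a "questionnaire of food items given to the baby in the last 24 h and one week preceding inquiry" and adds: "Study outcomes will be evaluated at weeks 2, 6, 10, and 24". Data collection and management says: "We will inquire about feeding practices during the previous 24 h and during the prior week". Adherence is defined there only for exclusive breastfeeding (breast milk and nothing else). Row 1d and the 70% criterion speak of breastfeeding adherence without saying exclusive or any.

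The Secondary outcomes text of the Analysis plan also commits to Kaplan–Meier and Cox analyses of "the cumulative proportions of women stopping exclusively breastfeeding", and of the same quantity for any breastfeeding. Row 2b, time to stopping breastfeeding, has its own measure: the woman's report that she has stopped completely.

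**The concern.** A cumulative outcome needs feeding information from birth to week 24. A recall of the last day or week describes feeding around the visit. Table 1 pairs the first label with the second measure, while the criterion is worded as a rate at one time point. An analyst could therefore compute two different quantities and set either against the 70% threshold, which is one of the conditions for going on to a larger trial. Table 1 also names two recall periods for one binary outcome. A woman can be adherent over the last 24 h and not over the week, and nothing says which recall decides.

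The second issue is timing. An analysis of time to stopping exclusive breastfeeding needs the age at which other food was first given. The only exclusive-feeding measure described yields a status at four visits, not an age.

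**Working it through.** **The plan's own figures.** Recruitment: 5 per week × 12 weeks = 60, as stated. With 1:1 allocation, 30 per arm, so the 70% criterion means 0.70 × 30 = 21 women. The article gives no figure for how much of follow-up the recalls cover.

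**Coverage.** Inputs: visits at weeks 2, 6, 10 and 24, and a recall of the preceding week (Secondary endpoints; Data collection and management).

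| Visit (week) | Recall window (weeks after birth) | Unobserved since previous visit | Longest possible dating error |
|---|---|---|---|
| 2 | 1 to 2 | 1 week | 2 weeks |
| 6 | 5 to 6 | 3 weeks | 4 weeks |
| 10 | 9 to 10 | 3 weeks | 4 weeks |
| 24 | 23 to 24 | 13 weeks | 14 weeks |

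Observed: 4 × 7 = 28 of 24 × 7 = 168 days, or 16.7%. Unobserved: 1 + 3 + 3 + 13 = 20 weeks. With the 24-h recall alone: 4/168 = 2.4%. The dating error is the interval between visits, for example 24 − 10 = 14 weeks, if the change is dated to the visit at which it is first seen.

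**What three feeding histories would record.**

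- Other food in week 15 only, then exclusive breastfeeding again: adherent at all four visits. A week-24 rate is right; a cumulative exclusive rate is wrong.
- Other food from week 15 onward: adherent at weeks 2, 6 and 10, non-adherent at week 24. The status is right under either reading, but the change is dated about 24 − 15 = 9 weeks late.
- Complete cessation of breastfeeding: covered by row 2b's own measure, not by the food recall.

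So the recalls misclassify only the first group, and only for a cumulative exclusive outcome. For the second group the error lies in the date.

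**Illustration of the first group (assumptions, not trial data).** Suppose one lapse of length L weeks with a uniformly distributed start. It is caught if it overlaps any one-week window.

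- If every lapse must end by week 24, starts lie in 0 to 24 − L. For L = 1: (2 + 2 + 2 + 1)/23 = 7/23 = 30% caught. For L = 4: (10 + 1)/20 = 11/20 = 55%.
- If lapses may still be running at week 24, starts lie in 0 to 24. For L = 1: (2 + 2 + 2 + 2)/24 = 8/24 = 33%. For L = 4: (10 + 5)/24 = 15/24 = 62.5%.

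These are chances of catching one assumed lapse. They are not a bias in the adherence rate, because the article does not say how many women lapse and resume.

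**Timing.** The Background reports that in the investigators' cohort half of the women who chose breastfeeding had switched to formula by roughly four months, about 4 × 52/12 = 17 weeks. That lies in the gap between weeks 10 and 23. A change at that time would first appear at week 24, about 7 weeks late, and the recalls could only place it between the week-10 visit and the week-24 window.

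**The case against.** The strongest reply is that this is a slip in one table label. Primary endpoints and the abstract both set the criterion at a point in time, and for a week-24 rate a recall ending at week 24 is a fitting measure. This stands. A reader might infer that the rate compared with 70%, and hence the planning rate for the main trial, would be too high. That follows only under a cumulative exclusive reading, and nothing in the article says that the main trial wants uninterrupted exclusive breastfeeding.

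A reader might also infer that every woman who gave other foods between visits is counted as adherent, or that the difficulty arises for any feeding category. Neither holds. Women who continue with other foods are found at the next visit, and the only pattern that the Background describes is a switch. If row 1d means any breastfeeding, brief other feeds do not change status, and stopping has a separate measure in row 2b.

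Finally, the questionnaire is not shown and may ask when other foods began, so reading the exclusive-breastfeeding times as coming from these recalls is an inference. That is a fair caution. Still, the three places that describe the feeding measure name only the two short recalls. The weekly text message asks about problems, in the intervention arm only, and is not described as a feeding record.

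The reply does not remove the printed mismatch in row 1d, the two recalls for one binary outcome, or the lack of any described source for the date at which exclusive breastfeeding stopped.

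**Conclusion.** The point holds in a limited form. Row 1d and the 70% criterion describe different quantities and must be reconciled. As described, the recalls give point prevalence over 4 of 24 weeks. They cannot give a cumulative exclusive-breastfeeding rate, and they cannot date the stopping of exclusive breastfeeding more closely than the visit interval, which reaches about 14 weeks after week 10. Misclassification is confined to women who gave other foods solely outside the recall weeks and then resumed; its size is unknown, because the article gives no frequency for that pattern. The conclusion does not extend to a week-24 rate or to time to stopping any breastfeeding. It assumes that the questionnaire holds no item on age at first other food; if it does, the dating problem is solved by saying so. The article reports that recruitment has not started, so the change can still be made before data are collected, whereas unasked weeks cannot be reliably recovered afterwards.

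**What to change.** 1. Relabel row 1d as point-prevalence adherence at week 24, matching Primary endpoints. State whether exclusive or any breastfeeding is meant. Name the one-week recall as the deciding measure and report the 24-h recall separately. The 70% threshold stays as written.

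2. Add one item to the questionnaire at each visit: since birth (first visit) or since the last visit, has the baby been given anything other than breast milk, and if so, at what age first? Use that age in the Kaplan–Meier and Cox analyses of stopping exclusive breastfeeding. Without the item, treat those times as interval-censored between visits.

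3. Report cumulative exclusive breastfeeding (no other food reported at any visit) as an additional descriptive outcome, not as the 70% criterion.

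Cost: one question per visit and a change of wording in Table 1. The downside is less exact recall over the longest interval, up to 14 weeks.
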